#### Outcome analysis

For the primary outcome, the total number and proportion of patients tolerating four months of treatment will be reported alongside the associated 95% credible interval, using the total number of patients who started combination therapy as the denominator (including patients who failed to find any tolerable dose). Bayesian posterior probability plots will be presented alongside the probability that the true tolerability rate is greater than 70%.

Analyses of the secondary and exploratory outcomes will be descriptive in nature, with no hypothesis testing conducted.The total number and proportion of patients tolerating up to two years of combination therapy will be reported alongside the associated 95% credible interval, using the total number of patients who started combination therapy as the denominator.Best overall response rate will be presented as the number and proportion of patients achieving a response, overall and by response category, over the total number of patients receiving combination treatment.The number and proportion of patients will be reported against the highest tolerated ropeginterferon alfa-2b dose that each individual patient received, having followed dose escalation schedule.Toxicity will be presented as the number and proportion of patients experiencing one or more grade ≥ 3 AEs, or a SAE of any grade. This outcome will be analysed using the safety population.Overall and progression-free survival will be presented using Kaplan–Meier plots. The median time to event and survival estimates at one year will be presented with 95% confidence intervals where appropriate.The MFSAF v4.0 analyses will be presented as medians with interquartile ranges over time. Multi-level models may be used to compare changes in scores from baseline to 12 months if appropriate.Bone marrow fibrosis will be tabulated and presented graphically, with number and proportion of patients at each level reported. In addition to this, individual patient results will be plotted to show change over time at the patient level.The *JAK2*^V617F^ mutant allele frequency will be presented as medians and interquartile ranges over time, overall and split by highest dose of ropeginterferon alfa-2b tolerated and summarised using descriptive statistics. Individual patient plots will also be presented showing raw percentages.

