### Statistical analysis plan

#### Sample size

The sample size for FEDORA is 30 patients. For the fedratinib plus ropeginterferon alfa-2b combination treatment to be considered acceptable, 80% of patients would need to tolerate treatment. If 60% or fewer patients tolerated treatment, then the combination would be considered unacceptable. Based on this, if there is a high probability that the true tolerability rate is greater than 70% then the treatment would warrant further investigation. Employing a conjugate beta-binomial analysis, with a minimally informative Beta(1,1) prior, if 23 of the 30 patients tolerate the treatment combination we would be 76% sure that the true tolerability is greater than 70%, and therefore warrant further investigation (Appendix 7).

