#### Interim and final analysis

No formal interim or pre-defined sub-group analyses are planned. Accumulating data and analyses will be monitored regularly by the TSC on a nine-monthly basis, or more frequently if required to monitor safety, recruitment, data quality, and activity. Final analysis of all outcome measures will be performed after all patients have completed a minimum of two years follow-up.

All analysis will be modified intention to treat (mITT) unless otherwise specified, with all patients who are recruited into the trial that receive at least one cycle of combination therapy included, irrespective of trial deviations and discontinuations. Patients who commence pre-treatment with fedratinib, but who do not then go on to receive concurrent ropeginterferon alfa-2b for any reason, or those who withdraw from the trial before the four-month primary outcome time-point for reasons unrelated to treatment toxicity or tolerability will be deemed unevaluable and replaced, and not included in the mITT analysis. Sensitivity analysis of outcomes will consider patient compliance with the treatment schedule and patients who do not receive at least one cycle of combination treatment.

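### The primary analysis set is defined in two incompatible ways for patients who start the combination and withdraw before four months for reasons unrelated to toxicity

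*Protocol article*

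**What the plan says.** All the relevant text is in the protocol article.

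- **Sample size.** "The sample size for FEDORA is 30 patients". The acceptable standard is that "80% of patients would need to tolerate treatment", and "If 60% or fewer patients tolerated treatment, then the combination would be considered unacceptable". The decision is framed as a posterior statement: "if there is a high probability that the true tolerability rate is greater than 70% then the treatment would warrant further investigation". The boundary case is "if 23 of the 30 patients tolerate the treatment combination we would be 76% sure that the true tolerability is greater than 70" per cent, which is said to be enough to warrant further investigation.
- **Interim and final analysis.** Modified intention to treat (mITT) is the default set and requires at least one cycle of combination therapy, unless a different set is specified. Two groups are replaced and left out of it. The first is patients who never receive ropeginterferon alongside fedratinib. The second is described as "those who withdraw from the trial before the four-month primary outcome time-point for reasons unrelated to treatment toxicity or tolerability will be deemed unevaluable and", with the sentence going on to their replacement.
- **Outcome analysis.** The number and proportion tolerating four months of treatment is reported "using the total number of patients who started combination therapy as the denominator (including patients who failed to find any tolerable dose"), together with the posterior probability that the true rate exceeds 70%.
- **Trial outcomes.** Not tolerating means stopping either drug because of drug-related toxicity, a toxicity-related delay of more than 28 consecutive days, or a toxicity-related death, within four months of starting the combination.

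**The concern.** Take a patient who receives ropeginterferon, then leaves the trial in month 2 for a reason that has nothing to do with toxicity. Under Interim and final analysis this patient is unevaluable and a replacement is recruited. Under Outcome analysis, read as written, the patient started the combination and so stays in the denominator next to the replacement.

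The patient's outcome is also unsettled. They have not tolerated four months of treatment, so they cannot enter the numerator. Yet nothing that happened to them meets the Trial outcomes definition of not tolerating. In a plain proportion, being in the denominator and outside the numerator has the effect of a failure, so a withdrawal unrelated to the drugs is charged against their tolerability.

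The stake is the posterior probability that tolerability exceeds 70%, which is the article's stated basis for further investigation. Two analysts who each follow the article faithfully could report different values from identical data. With about 30 patients, one or two such withdrawals are enough to matter.

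**Working it through.** **Inputs.** From Sample size: N = 30, boundary count 23, target rate 0.70, acceptable rate 0.80, unacceptable rate 0.60, and the model ("Employing a conjugate beta-binomial analysis, with a minimally informative Beta(1,1) prior"). Assumed: k, the number of patients who start the combination, withdraw before four months for unrelated reasons and are replaced. The article gives no rate for this, so k = 1 to 3 is shown.

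**Step 1: reproduce the printed figure.** With x tolerating out of n, the posterior is Beta(1 + x, 1 + n − x), and

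P(rate > 0.70) = 1 − F(0.70; 1 + x, 1 + n − x), where F is the beta distribution function.

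For 23 of 30 this is Beta(24, 8), which gives 0.755. That agrees with the printed 76%.

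**Step 2: follow the Outcome analysis denominator literally.** There are 30 evaluable patients after replacement, 23 of whom tolerate treatment. The k replaced patients are added to the denominator and not to the numerator, so n = 30 + k.

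| k | x / n | Posterior | P(rate > 0.70) |
|---|---|---|---|
| 0 | 23 / 30 | Beta(24, 8) | 75.5% |
| 1 | 23 / 31 | Beta(24, 9) | 65.6% |
| 2 | 23 / 32 | Beta(24, 10) | 55.0% |
| 3 | 23 / 33 | Beta(24, 11) | 44.6% |

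**Step 3: effect on the chance of a favourable decision.** Hold the decision level at the posterior that 23 of 30 gives (0.755). The smallest count reaching that level is 23 of 30, 24 of 31, 25 of 32 and 26 of 33. The next count down falls short each time: 22/30 gives 0.614, 23/31 gives 0.656, 24/32 gives 0.696 and 25/33 gives 0.732. All the tolerating patients must come from the 30 evaluable ones, so with X ~ Binomial(30, 0.80):

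| k | Count needed among 30 evaluable | P(favourable decision) at true 80% |
|---|---|---|
| 0 | 23 | 76.1% |
| 1 | 24 | 60.7% |
| 2 | 25 | 42.8% |
| 3 | 26 | 25.5% |

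**Step 4: look for text that reconciles the two rules.** The exception clause attached to mITT lets Outcome analysis depart from that set, but does not say whether replaced patients come back. The parenthesis in Outcome analysis concerns patients who found no tolerable dose, who are toxicity failures and not unrelated withdrawals. The planned sensitivity analyses cover compliance and patients with less than one cycle of the combination. They do not clearly cover a patient who completes a cycle and then withdraws for an unrelated reason.

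**The case against.** The best counter-argument is that the two sections can be read together. For toxicity, Outcome analysis departs from mITT by naming another set, the safety population. For the primary outcome it names none. Its denominator wording could therefore serve only to exclude patients who had fedratinib alone and to keep toxicity failures, with the replacement rule still removing unevaluable patients. That reading is possible, and under it the problem disappears. But the article does not state it, and the literal words say otherwise, so the wording still needs to be reconciled.

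Three stronger readings might be inferred, and the article does not support them.

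- *That N will exceed 30.* This requires at least one unrelated withdrawal after the combination has started. Patients who never receive ropeginterferon are outside both denominators and do not add to N.
- *That the 76% is wrong.* It is correct for 23 of 30. The posterior is to be reported from the data, so a different N simply yields a different figure.
- *That the ambiguity also raises the chance of accepting a poorly tolerated combination.* This would need replaced patients to be scored as tolerating and the bare count of 23 to be kept at a larger N. The numerator of patients tolerating four months gives little support for the first, and the article frames the decision as a posterior probability, not a fixed count. At the 0.755 level, even with replaced patients scored as tolerating, 24 of 31, 25 of 32 and 26 of 33 each still require 23 of the 30 evaluable patients. The chance of a favourable decision at a true 60% then stays at 4.4% for k = 1 to 3.

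**Conclusion.** The concern holds as an inconsistency in a stated rule for the primary analysis, not as detail that an article may leave to a fuller document. One section excludes and replaces a group of patients whom the other, read literally, counts in the denominator with no outcome category that fits them.

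The effect runs towards understating tolerability. One such patient lowers the posterior at the boundary by about 10 percentage points (75.5% to 65.6%), and two bring it close to even odds. These sizes rest on three assumptions: the value of k, a literal reading of the Outcome analysis denominator, and the 23-of-30 posterior as the level for a favourable decision. If k is 0, or if the replacement rule is meant to govern the primary outcome as well, there is no numerical effect. The correction should be made before the final analysis, so that the choice of set cannot depend on the results.

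**What to change.** In Outcome analysis, define the primary denominator as patients who started combination therapy. Keep every toxicity failure from the first ropeginterferon dose onward, including those in cycle 1, and leave out only patients deemed unevaluable and replaced under Interim and final analysis. Use the same definition in both sections.

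Report all patients who started the combination, with replaced patients counted as not tolerating, as a sensitivity analysis.

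State that the decision uses the posterior level given by 23 of 30 (0.755), applied to the N actually analysed, so that it still works if N is not exactly 30.

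The cost is one or two sentences and one extra beta-binomial calculation, with no additional patients. The small downside is that the primary rate becomes conditional on not withdrawing for unrelated reasons, which the sensitivity analysis makes visible.

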### Interventions

Table 2 provides an overview of a patient’s journey during the FEDORA trial.

**Table 2 Tab2:** FEDORA trial schedule of events

Assessment		Screening (within 60 days of registration)	Fedratinib pre-treatment Up to 3 cycles		Combination treatment					End of treatment visit^b^	
					Cycles 1–2		Cycle 3	Cycles 4 +	Follow-up on treatment		
			Day 1	Day 15	Day 1	Day 15	Day 1	Day 1	(Month indicated)^a^		
Informed consent		x									Follow up 3-mothly after treatment for survival, progression and subsequent treatment
Demographic data and medical history		x									
Clinical & physical assessment (Height^c^, weight, ECOG status, blood pressure, pulse, oxygen sats, respiratory rate, physical examination, fundoscopy^c^)		x	x	x	x	x	x	x		x	
ECG		x									
Pregnancy test^d^		x	x		x		x	x		x	
Laboratory Tests	Haematology^e^	x	x	x	x	x	x	x		x	
	Blast count/percentage^f^	x	x	x	x	x	x	x		x	
	Blood film assessment	x							6, 12, 18, 24		
	Biochemistry^g^	x	x	x	x	x	x	x		x	
	Coagulation^h^	x	x		x		x		6, 9, 12, 15, 18, 21, 24		
	Thiamine (vitamin B1) testing	x	After every 3 months of fedratinib treatment								
	Virology^i^	x									
	*JAK2*^V617F^ assessment^j^	x									
Spleen assessment	Palpation	x	x		x		x	x			
	Ultrasound	x							6, 12, 18, 24		
Bone marrow aspirate and trephine		x							6, 12, 18, 24		
Peripheral blood and serum samples for research, including *JAK2*^V617F^ clone size		x			D1 C2 only		x		6, 9, 12, 15, 18, 21, 24		
DIPSS score		x									
MFSAF		x							3, 6, 9, 12, 15, 18, 21, 24		
Disease response assessment (IWG criteria)									6, 12, 18, 24		
WHO bleeding score		x	x		x		x	x			
Fedratinib administration			Daily throughout the trial								
Ropeginterferon alfa-2b administration					Day 1 and 15 of each cycle, starting from Cycle 1						
Thiamine supplementation			Daily, alongside fedratinib treatment								
Transfusion assessment		x	Monitored continuously								
Concomitant medication			Monitored continuously								
Adverse events		x^k^	Monitored continuously								

*DIPSS* dynamic international prognostic scoring system, *ECG* echocardiogram, *ECOG* Eastern Cooperative Oncology Group, *IWG* internal working group, *MFSAF* myelofibrosis symptom assessment form, *WHO* World Health Organization

^a^Within 14 days of time-points indicated

^b^To be completed 28 days after last dose of protocolised drug

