### Dose modifications, delays, and discontinuations

Patients should discontinue trial treatment in the following circumstances:Stopped by an investigator for clinical reasons not related to the study drug treatment.Any unforeseen event which, in the judgement of the investigator, makes further treatment inadvisable.Serious violation of the study protocol, including persistent patient non-attendance and persistent non-compliance.If the patient becomes pregnant or is a patient of child-bearing potential who fails to use adequate birth control.Serious adverse event (SAE) requiring permanent discontinuation of treatment.Development of unacceptable side effects.Confirmed disease progression (spleen size increase from baseline of > 5cm, increase in bone marrow fibrosis, or peripheral blood or bone marrow blasts ≥ 20%).At the request of the patient.

In the event of an overdose of either fedratinib or ropeginterferon alfa-2b, treatment should be paused, the patient closely monitored, and supportive measures provided as necessary. Any overdose with or without associated adverse effects (AEs) or SAEs is required to be reported within 24 h of first knowledge of the event to the Trial Office.

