### Trial outcomes

The primary outcome is tolerability of combination therapy. A patient is classified as not tolerating treatment if they discontinue either fedratinib or ropeginterferon alfa-2b due to drug-related toxicity, due to delays in treatment exceeding 28 consecutive days due to drug-related toxicity, or if a treatment toxicity-related death is reported, within four months of starting combination therapy.

The secondary outcomes are:Tolerability of combination therapy throughout the treatment course. A patient is classified as not tolerating treatment as per the definition for the primary outcome.Best overall response (complete plus partial response) assessed using International Working Group criteria (spleen size measure by palpation) [30] within 12 and 24 months from starting combination treatment. Patients who die or do not have a disease response recorded prior to the relevant time points will be classified as non-responders.The highest tolerated dose of ropeginterferon alfa-2b, in combination with fedratinib, achieved by each patient. To be tolerated, the dose must have been maintained for at least one complete cycle.Toxicity, defined to be any grade ≥ 3 AE, or a SAE of any grade. See the Adverse Events Reporting and Analysis section for details.Overall survival, defined as the time from starting combination therapy to date of death from any cause. Patients who are alive at the time of analysis or lost to follow-up will be censored at their date last seen.Progression-free survival, defined as the time from starting combination therapy to first event or death from any cause. An event is defined to be any of the following: an increase in bone marrow fibrosis, an increase in spleen size by > 5cm, or transformation to acute myeloid leukaemia. Patients who are alive and event-free at the time of analysis or lost to follow-up will be censored at their date last seen.Quality of life assessed using the myelofibrosis symptom assessment form (MFSAF) v4.0 [31] total symptom score at trial entry, and three-monthly during treatment.Bone marrow fibrosis, assessed using consensus definitions [32] at trial entry and six-monthly during treatment.

The *JAK2*^V617F^ clone size, measured at trial entry and three-monthly during treatment, is an exploratory outcome.

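### MFSAF medians at each visit describe a changing set of patients, and the within-patient model that would limit this is only optional

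*Protocol article*

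**What the plan says.** All references are to the protocol article.

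- **Collection.** Trial outcomes defines the measure as the MFSAF "total symptom score at trial entry, and three-monthly during treatment". In the schedule of events (Table 2) every MFSAF time after screening, months 3 to 24, is in the on-treatment follow-up column, and the row has no end-of-treatment entry. After treatment the table lists only "Follow up 3-mothly after treatment for survival, progression and subsequent treatment".
- **Analysis.** Outcome analysis states "The MFSAF v4.0 analyses will be presented as medians with interquartile ranges over time", then "Multi-level models may be used to compare changes in scores from baseline to 12 months if appropriate". The first sentence is a commitment. The second is optional and stops at 12 months, although scores are scheduled to month 24.
- **Stopping.** Reasons to end treatment include "Development of unacceptable side effects", "Confirmed disease progression (spleen size increase from baseline of > 5cm" and other progression criteria, serious adverse events and patient request.
- **Population.** The modified intention-to-treat set keeps patients "irrespective of trial deviations and discontinuations" once they have had a cycle of combination therapy. Patients who withdraw before four months for reasons unrelated to toxicity or tolerability are excluded and replaced.
- **Status.** "Analyses of the secondary and exploratory outcomes will be descriptive in nature, with no hypothesis testing conducted".

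**The concern.** A series of medians is read as a course over time. It can be read that way only if much the same patients stand behind each point. Here the baseline median covers the whole analysis set, while the month-12 median covers those still on treatment and still completing the form. If those who left had worse symptoms, the later median is lower because of who remains.

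Keeping discontinued patients in the analysis set does not help, because no later MFSAF score is scheduled for them. A single arm has no control group in which the same drift would show. The article handles the problem better elsewhere: patients with no recorded response count as non-responders, tolerability uses everyone who started the combination as denominator, and individual-patient plots are promised for marrow fibrosis and *JAK2* allele frequency. MFSAF has no such committed safeguard.

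At stake is the reading of one descriptive secondary outcome.

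**Working it through.** **The plan's own figures.** The article gives none for MFSAF. Its one design figure, 76% for 23 of 30 tolerating, reproduces: the posterior is Beta(24, 8) and P(rate > 0.70) = 0.755. This point does not affect it.

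**Inputs.** From the article: n = 30, single arm. Assumed: score mean 20, SD 10 to 12, no true mean change, baseline to follow-up correlation 0.6. Dropout of 20 to 40% is also assumed. The nearest guide is the sample-size section, where 80% tolerability is acceptable and 60% or less is not. That guide is loose, because stopping one drug need not end all treatment.

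**Hand calculation.** Let a fraction d leave, namely those highest on a normal dropout tendency that has correlation r with the follow-up score. The mean score of those remaining shifts by

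shift = −SD × r × φ(z)/(1 − d), where z is the (1 − d) normal quantile.

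The last factor is 0.280/0.8 = 0.350 at d = 0.2, 0.348/0.7 = 0.497 at d = 0.3, and 0.386/0.6 = 0.644 at d = 0.4.

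- Mild link, low end: 10 × 0.3 × 0.350 = 1.05, a fall of about 1 point.
- Moderate link, high end: 12 × 0.5 × 0.644 = 3.86, a fall of about 4 points.
- Strong link, high end: 12 × 0.707 × 0.644 = 5.46, a fall of about 5.5 points.
- No link: r = 0, shift 0.
- Reversed link at 30%: −12 × (−0.3) × 0.497 = +1.8, an apparent worsening.

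**Simulation of the planned display.** n = 30, 8000 replicates, mean 20, SD 12, scores clipped to 0–70, correlation 0.6. The dropout tendency is the standardised score plus noise of equal variance, so its correlation with that score is 1/√2 = 0.707. When it acts on baseline, the correlation with the follow-up score is 0.6 × 0.707 = 0.424. The median shift is the follow-up median of those remaining minus the baseline median of all 30. The adjusted change regresses follow-up on baseline in those remaining and predicts at the mean baseline of all 30.

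| Dropout depends on | Dropout | Median shift | Unadjusted median paired change | Baseline-adjusted change |
|---|---|---|---|---|
| nothing | 20 / 30 / 40% | 0.0 / 0.0 / 0.0 | 0.0 / 0.0 / 0.0 | 0.0 / 0.0 / 0.0 |
| baseline score | 20 / 30 / 40% | −1.7 / −2.4 / −3.1 | +1.0 / +1.5 / +1.9 | 0.0 / 0.0 / +0.1 |
| current, unobserved score | 20 / 30 / 40% | −2.6 / −3.8 / −5.1 | −1.1 / −1.5 / −1.9 | −2.0 / −2.8 / −3.8 |

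The hand formula for the mean gives 1.8, 2.5 and 3.3 for the baseline rows and 3.0, 4.2 and 5.5 for the current-score rows, close to the simulated median shifts.

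**What the table shows.** The drift appears only when dropout is related to symptoms. Baseline adjustment removes it when dropout depends on observed scores. When dropout depends on unobserved scores it removes only about a quarter: 1 − 1.98/2.61 = 24%, 1 − 2.83/3.82 = 26%, 1 − 3.75/5.12 = 27%. Unadjusted paired change is not a safe substitute: when high baseline scorers leave, regression to the mean makes it rise by 1 to 2 points.

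**The case against.** Four points can be made for the plan.

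1. **The article already names the model, and the rest is analysis-plan detail.** Missing-data rules and model specification may well be in a statistical analysis plan that is not shown, and their absence is not the point here. What stands against the plan is its own ranking of the two analyses: medians committed, within-patient model optional and cut at 12 months. Making the model conditional is understandable with 30 patients and a bounded score, since fits of this size can fail to converge. That argues for a simple model, not for leaving it open.

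2. **Selective dropout need not look like improvement.** A reader might infer that the plan will show falling symptoms. The documents do not support that. They give no dropout rate and no link between stopping and symptoms, and the listed progression criteria are spleen size, fibrosis and blasts rather than a symptom score. The drift may be downward, nil or upward. At n = 30 the trial-to-trial SD of the median shift is also about 3 points, similar to the bias itself. This objection stands.

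3. **Little rests on MFSAF.** A reader might take it as a main activity signal. The Discussion instead places evidence of activity in best overall response and progression-free survival, and the only stated criterion for going further is tolerability above 70%. This also stands.

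4. **Not every patient who leaves stays in the baseline median.** Patients without a cycle of combination therapy, and those who withdraw before four months for reasons unrelated to toxicity or tolerability, are outside the analysis set altogether. The mismatch is therefore confined to patients who stay in the set and stop treatment: toxicity stops after the first cycle, and later stops for any reason.

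**Conclusion.** The point holds in a conditional form. As written, the committed MFSAF display can compare different patients at different visits, and the analysis that would limit this is optional. If stopping treatment is related to symptoms, the medians can drift by about 1 to 4 points with no true average change, on an assumed mean of 20, SD 10 to 12, 20 to 40% dropout and a mild to moderate link. The strongest setting tried reached 5.1. The drift is zero if dropout is unrelated to symptoms, and reversed if less symptomatic patients leave. None of these inputs is in the article, so the sizes are illustrative. The mismatch itself follows from the collection schedule and the stated analysis alone. The matter is minor: a descriptive secondary outcome, with no bearing on the tolerability decision.

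**What to change.** - Make a baseline-adjusted within-patient change from baseline the main descriptive MFSAF analysis: a multi-level model with a random patient effect, using all scheduled MFSAF visits to month 24, reported as an estimate with its interval. No test is needed, so the descriptive status of the outcome is kept.
- Keep the medians and interquartile ranges as a supporting display. Beside each, show the number of patients contributing and the baseline median of those same patients.
- State that the model does not remove bias from dropout that depends on unobserved scores.

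The cost is slightly more analysis work on data already scheduled for collection, and possibly a less favourable curve. Nothing changes in the visits, the sample size or the primary analysis.

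### Patients whose marrow fibrosis increases tend to leave the fibrosis table after the visit that detects it, so the by-visit proportions are biased favourably from month 12

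*Protocol article*

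**What the plan says.** Four places in the protocol article act together.

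- **Dose modifications, delays, and discontinuations.** The list opens "Patients should discontinue trial treatment in the following circumstances", and one entry is "Confirmed disease progression (spleen size increase from baseline of > 5cm, increase in bone marrow fibrosis", followed by a blast threshold.
- **Trial outcomes.** The secondary outcome is "Bone marrow fibrosis, assessed using consensus definitions [32] at trial entry and six-monthly during treatment".
- **Interventions, Table 2.** Marrow aspirate and trephine appear at screening and at months 6, 12, 18 and 24 in the on-treatment follow-up column. After treatment the schedule gives "Follow up 3-mothly after treatment for survival, progression and subsequent treatment", with no marrow sample.
- **Outcome analysis.** "Bone marrow fibrosis will be tabulated and presented graphically, with number and proportion of patients at each level reported". The section adds that "individual patient results will be plotted to show change over time at the patient level".

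The general rule under Interim and final analysis is modified intention to treat (mITT), with discontinued patients retained. No denominator is given for fibrosis. For tolerability and best response the article does name the denominator, and for response it also says how patients without a recorded assessment are scored.

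**The concern.** The measurement stops because of the value measured. A patient found to have worsened at month 6 is counted as such at month 6. If treatment is then stopped as listed, that patient has no further scheduled marrow and is absent at months 12, 18 and 24. Stable and improved patients stay in. This loss depends on the outcome and follows from the protocol's own rules; it is not chance drop-out.

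A reader comparing the grade distribution at month 24 with that at entry would be comparing a selected group with the whole cohort. The table would understate fibrosis progression. Under some rates it would show a falling mean grade while fibrosis in the cohort was rising.

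**Working it through.** **Plan's own figure.** None is given for fibrosis. The article's one computed design figure, 76% for 23 of 30 tolerating, concerns the primary outcome. It reproduces (Beta(24,8) upper tail at 0.70 = 0.755) and has no bearing here.

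**Inputs from the article.** Four post-entry marrow visits (months 6, 12, 18, 24), 30 patients, and a fibrosis increase as a reason to stop.

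**Assumptions, because the article gives no rates.** Grades 0 to 3; entry mix 30/50/20% at grades 1/2/3, so the entry mean is 0.3×1 + 0.5×2 + 0.2×3 = 1.90. Moves are of one grade per six months with fixed probabilities up and down, and changes are persistent. A patient leaves after the first visit with a grade above entry. There is no other drop-out.

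**One case by hand: 15% up, 0% down.** Grade 3 cannot rise.

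- Still sampled at month 24 (not worsened by month 18): 0.2 + 0.8×0.85³ = 0.2 + 0.8×0.614 = 0.691, or 20.7 of 30.
- Mean grade in the table: (0.3×0.614×1.15 + 0.5×0.614×2.15 + 0.2×3) / 0.691 = 1.472/0.691 = 2.13.
- Full cohort, expected rise from grade 1: P(one move) + 2×P(two or more) = 0.368 + 2×0.110 = 0.588.
- Full cohort, expected rise from grade 2: 1 − 0.85⁴ = 0.478.
- Full-cohort mean: 1.90 + 0.3×0.588 + 0.5×0.478 = 2.315, or 2.32.

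**Month 24, exact Markov calculation, same entry mix** (entry: grade 3 20%, mean 1.90)

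| Up / down per 6 months | Still sampled | Grade 3: table vs cohort | Mean grade: table vs cohort |
|---|---|---|---|
| 5% / 5% | 89% | 20.6% vs 24.9% | 1.77 vs 1.86 |
| 10% / 10% | 80% | 20.8% vs 27.9% | 1.66 vs 1.82 |
| 15% / 10% | 72% | 24.8% vs 34.8% | 1.73 vs 1.95 |
| 15% / 0% | 69% | 35.6% vs 47.2% | 2.13 vs 2.32 |

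**Onset, 10% / 10%.** Grade 3 in table vs cohort is 23.0% vs 23.0% at month 6, 22.2% vs 25.2% at month 12, 21.4% vs 26.8% at month 18 and 20.8% vs 27.9% at month 24. The gap opens at month 12 and widens.

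**Another entry mix (20/45/35%, entry mean 2.15), month 24, table vs cohort.** 10% up/5% down: 2.11 vs 2.20, so the direction reverses. 15%/0%: 2.38 vs 2.48. 20%/5%: 2.26 vs 2.40.

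In every scenario run, the table was more favourable than full follow-up from month 12. Whether it fell or rose from entry depended on the rates.

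**The case against.** Several counter-arguments have force.

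- **The information is not lost.** A fibrosis increase is an event in progression-free survival (PFS), and the individual plots show the rise and the shortened series. Both are true. But PFS pools it with spleen growth, leukaemic transformation and death, so it gives no fibrosis-specific rate, and the plots leave the proportions as they are.
- **mITT covers all analyses, and a condensed article may leave table details to the SAP.** The point does not rest on a missing table shell. The stated stopping rule and schedule mean that later grades are not collected, and mITT cannot supply grades that were never measured.
- **Stopping is not absolute.** The list says that patients should discontinue, and progression must be confirmed. Some worsened patients may have a further on-treatment marrow, which would soften the effect.
- **The effect is not automatic.** A reader might infer that the table must look stable or improved by construction. It need not: newly worsened patients appear at the detecting visit, grade 3 patients cannot rise and so are never removed for this reason, and with 15% up and none down the table rises clearly. If grade changes were only reading error, there would be no drift to lower grades.
- **The outcome is not decisive.** A reader might infer that the phase III decision is distorted. The only quantified criterion is tolerability above 70%, and the Discussion names best overall response and PFS as the activity evidence, not fibrosis grade.

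**Conclusion.** The point holds in limited form. Read together, the rules tend to remove worsened patients from the fibrosis table after the detecting visit and bias the by-level proportions favourably from month 12. Month 6 is unaffected by this mechanism.

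The size is not known. Under the assumed 10% up/10% down it is about 7 percentage points at grade 3 by month 24, roughly two patients in 30. Under 15% up/10% down the sign of the change in mean grade reverses. These figures rest on persistent one-grade moves, the assumed entry mix, stopping at the first increase and no other drop-out. The documents do not support a claim that the table will show stability or improvement whatever happens, or that the tolerability decision is affected. Severity is minor to moderate: a secondary, descriptive outcome would be reported in a misleading form, and this can be corrected before the final analysis.

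**What to change.** Leave the biopsy schedule and the stopping rule as they are. Under Outcome analysis:

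1. Add a table of best and worst change from each patient's own entry grade (improved, stable, ever worsened), cumulative by visit, over all mITT patients.
2. Keep patients who stopped after a fibrosis increase in a category such as *worsened / discontinued for fibrosis increase* at all later visits.
3. Give separate rows for other progression, death, other discontinuation and no sample.
4. Label the by-level table as on-treatment only, with the number assessed at each visit.

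The ever-worsened row is a cumulative count, not the grade a patient would have had later, and should be labelled so. Under 10% up/10% down with the 30/50/20% entry mix it would reach 8.0 + 6.4 + 5.2 + 4.3 = 23.9% by month 24 (each term is the newly worsened share of all patients at that visit), against 20.4% above entry grade at month 24 itself with full follow-up.

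The cost is one extra table and a less favourable-looking result. No new biopsies or visits are needed.
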